## 9. Analysis plan

Prior to analyses, we will produce data summaries to assess data quality, data distribution, and randomization success. All analyses will be evaluated using an intention-to-treat approach. An individual will be classified as vaccinated if they uploaded documentation of vaccination within 2 weeks after the end of the first week of vaccination appointments.

We estimate that a sample of 1450 (725 per arm) will provide at least 90% power to detect a 5 percentage point difference in vaccination between the intervention and control groups. This assumes a 20% vaccination rate in the control group and uses a two-sided alpha of 0.05.

The primary analysis will use a chi-square test to evaluate for differences in vaccination rate between the intervention and control group. Differences in time to vaccination will be evaluated using a t-test for means and Mann-Whitney test for medians. We will test the robustness of these findings by fitting a fully adjusted model with available participant characteristics. We will perform exploratory subgroup analyses for available participant characteristics.

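### The planned 725 per arm gives about 63% power for 20% versus 25%, not at least 90%; 90% would need about 1,464 per arm

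*Combined protocol and SAP*

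**What the plan says.** The only sample-size justification is in Section 9 (Analysis plan). It estimates that "a sample of 1450 (725 per arm) will provide at least 90% power to detect a 5 percentage point difference in vaccination" between the two arms. The next sentence supplies the remaining inputs: "This assumes a 20% vaccination rate in the control group and uses a two-sided alpha of 0.05".

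The same section fixes the test: "The primary analysis will use a chi-square test to evaluate for differences in vaccination rate between the intervention and control group". Section 2 (Overall objectives) sets the direction, an increase in vaccination, so the planned comparison is 20% in control against 25% in the intervention arm. Section 9 mentions no allowance for dropout, no interim analysis and no power calculation based on covariate adjustment. The adjusted model appears there only as a robustness check.

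**The concern.** A 5-point difference from a base of 20% usually calls for well over 1,000 participants per arm at 90% power, so 725 per arm looked too small by about half.

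This matters because the figure concerns the primary outcome, and readers will use it to judge a non-significant result. A trial with at least 90% power that finds nothing gives fairly strong evidence against a 5-point effect. A trial with about 63% power does not. The protocol also attaches a consequence to the result: under Section 8.2 (Procedures), the control arm is offered the text messages only if the approach proves successful. If that judgement follows the primary test, a false negative would withhold a working approach from the controls.

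**Working it through.** **Inputs**, all from Section 9 except the direction (Section 2):

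- n = 725 per arm, 1:1 allocation
- p1 = 0.20 (control), p2 = 0.25 (intervention), difference d = 0.05
- two-sided alpha 0.05, so z = 1.960
- chi-square test of two independent proportions

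**Step 1: power at the stated sample size.** The standard formula, with pooled variance under the null, is

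power = Φ[(d − 1.960 × SE0) / SE1], where SE0 = √(2p̄(1 − p̄)/n) and SE1 = √((p1(1 − p1) + p2(1 − p2))/n).

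- p̄ = (0.20 + 0.25)/2 = 0.225, so 2p̄(1 − p̄) = 2 × 0.225 × 0.775 = 0.34875
- p1(1 − p1) + p2(1 − p2) = 0.1600 + 0.1875 = 0.3475
- SE0 = √(0.34875/725) = 0.02193
- SE1 = √(0.3475/725) = 0.02189
- (0.05 − 1.960 × 0.02193)/0.02189 = 0.320
- Φ(0.320) = **0.626**

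The plan's figure of at least 90% is not reproduced.

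**Step 2: does the choice of method matter?** At 725 per arm, 20% versus 25%, two-sided 0.05:

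| Method | Power |
|---|---|
| Normal, pooled variance | 62.6% |
| Normal, unpooled variance | 62.7% |
| Arcsine | 62.7% |
| Chi-square, exact enumeration | 62.7% |
| Chi-square with continuity correction, exact enumeration | 60.2% |

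**Step 3: do more generous readings reach 90%?** Still at 725 per arm:

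| Reading | Power |
|---|---|
| One-sided alpha 0.05, contrary to the text | 73.8% |
| 20% versus 15% | 70.8% |
| 20% versus 15% and one-sided 0.05 | 80.6% |

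None does.

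**Step 4: sample size for 90% power.**

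n = (1.960√0.34875 + 1.2816√0.3475)² / 0.05² = (1.1575 + 0.7555)² / 0.0025 = 1,463.7, so **1,464 per arm, 2,928 in total**.

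The unpooled and arcsine versions give 1,461 and 1,462 per arm, and the continuity-corrected version 1,504. For 80% power, replacing 1.2816 with 0.8416 gives 1,094 per arm.

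**Step 5: what 725 per arm can detect.** With the control rate held at 20%, solving the Step 1 formula for d gives about 7.2 points for 90% power (20% versus 27.2%) and about 6.2 points for 80% power.

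**Step 6: where the figure could have come from.** The plan does not say. Three candidates come close:

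- 1,450 taken per arm: SE0 = 0.01551, SE1 = 0.01548, (0.05 − 1.960 × 0.01551)/0.01548 = 1.266, power 89.7%.
- A one-sample formula against a fixed 20%: n = (1.960√0.16 + 1.2816√0.1875)²/0.05² = 717.1, so 718; 725 gives 90.3%.
- A control rate of about 7% in place of 20%: 7% versus 12% at 725 per arm gives 90.2%.

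**The case against.** The arithmetic itself has no defence: the total and the per-arm figure agree with each other, so this is not a misread number, and no other section changes the calculation. The reasonable objections concern what follows from it.

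First, the cause is not known. A per-arm number entered as the total is plausible, but the one-sample formula fits the words *at least* slightly better (90.3% against 89.7%), and a wrong control rate is also possible. This stands. The cause should be put as a question to the sponsor, and the error holds whichever slip occurred.

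Second, 725 per arm may not be what the trial enrols. Sections 5.4 and 6 leave the sample to the health system's list, and Section 5.1 leaves the choice of markets open, so actual power could be higher or lower. This also stands, but the sentence is about 1,450 participants, and for that number it is wrong.

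Third, 63% power is still better than an even chance, and the 37% risk of a miss applies to a true difference of exactly 5 points on a 20% base. That is a fair limit on the claim. It does not restore the stated figure, which was made for that same scenario and also falls short of the common 80% level.

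**Conclusion.** The power statement is wrong as written. With the plan's own inputs, power is about 63%, a shortfall of about 27 percentage points from the stated minimum (90 − 63). The risk of missing a true 5-point effect is about 37% (100 − 62.6 = 37.4), nearly four times the 10% implied. The sample needed for 90% power is about twice the one stated (2,928/1,450 = 2.02).

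This rests on 725 analysed per arm, a 20% control rate, a true rate of 25% under the intervention, independent outcomes and a two-sided 0.05 chi-square test. Apart from independence, which the planned chi-square test itself assumes, these are the plan's own inputs. The conclusion does not depend on the power formula chosen, and it needs no view on how the error arose.

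**What to change.** The sponsor should say which of the four figures in Section 9 (sample size, control rate, difference, power) is in error, and reconcile them.

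If 1,450 in total is right, replace the sentence with wording such as:

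> A sample of 1,450 (725 per arm) gives about 63% power for 20% versus 25%, and 90% power for a difference of about 7.2 percentage points (20% versus 27.2%), at two-sided alpha 0.05.

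If 1,450 per arm was intended, write 2,900 in total (1,450 per arm) with about 90% power. The words *at least* should then go, because the value is 89.7%; keeping them requires 1,464 per arm.

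In either case, add that a non-significant result will be interpreted through the 95% confidence interval for the risk difference. At 20% versus 25% with 725 per arm its half-width is about 1.960 × 0.02189 = 0.043, or 4.3 points, which shows readers the precision the trial offers.

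Restating the power costs one sentence and a less favourable stated figure, with no added participants. Actually reaching 90% power for 5 points would need about twice the sample. Section 6 describes no active recruitment, so a longer list may be possible, but the documents do not say how many eligible employees the chosen markets hold.

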## 4. Background

The COVID-19 pandemic has caused significant morbidity and mortality across the world. Effective vaccines are now available but underutilized. In July 2021, Ascension Health implemented a mandate requiring all employees to obtain the COVID-19 vaccine by November 12th. In August 2021, the number of COVID-19 cases in the US increased rapidly, specifically in states with lower vaccination rates, many of which are served by Ascension Health facilities.

Nudges are subtle changes to the way information is framed or choices are offered that can have a significant impact on behavior. Status quo bias is a preference for the current state which is often used as a reference point when making decisions. Changes from the reference point are often faced with high inertia and this prevents changes in behavior. Default options are the setting of the baseline reference point and are often taken as an implicit recommendation.

In prior work, changing default options has led to significant changes in health-related behaviors. For example, changing prescription default settings in the EHR from opt-in to opt-out for generic prescriptions increased the rate of generic prescriptions from 75% to 98% across Penn Medicine (Patel et al. *Annals of IM*. 2014; Patel et al. *JGIM* 2018). Framing program participation as opt-out has led to a 22% increase in enrollment in a COVID-19 surveillance testing program (Oakes et al. *NEJM Catalyst* 2021) and triple enrollment in remote monitoring programs for medication adherence (Mehta et al. *JAMA Cardiology*. 2018) and diabetes management (Aysola et al. *AJHP* 2016)

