## 5. Study Design

### 5.1 Design

This will be conducted as a two-arm randomized, controlled trial. The control arm will receive usual health system messaging about the importance and deadlines for receiving COVID-19 vaccination. The intervention arm will receive a text message stating that the vaccine is reserved for them on a specific date. They will have the ability to reschedule to a different day, opt-out of this text messaging intervention, or if previously vaccinated they can upload documentation to the Ascension website.

A list of Associates for whom Ascension does not have documentation of vaccination or exemption from vaccination will be provided by Human Resources at Ascension. Information on vaccine clinic locations and hours are available online and a link to them will be provided in the text message.

Participants sites will likely include Ascension Associates from the following markets: DC, Maryland, NY Binghamton, Kansas and/or Florida

The trial is anticipated to begin around: September 13, 2021.

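### Making a pre-specified covariate-adjusted analysis primary, with the chi-square kept beside it, would be a small, near-free gain in precision

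*Combined protocol and SAP*

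**What the plan says.** Section 9 sets the primary comparison: "The primary analysis will use a chi-square test to evaluate for differences in vaccination rate between the intervention and control group". Covariates appear only afterwards: "We will test the robustness of these findings by fitting a fully adjusted model with available participant characteristics". The plan does not list those characteristics, name the type of model or give the effect measure it will report. It does not mention market as a covariate.

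On size, Section 9 says: "We estimate that a sample of 1450 (725 per arm) will provide at least 90% power to detect a 5 percentage point difference in vaccination". It adds: "This assumes a 20% vaccination rate in the control group and uses a two-sided alpha of 0.05". On the analysis set: "All analyses will be evaluated using an intention-to-treat approach".

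Section 5.1 (Design) expects participants from "DC, Maryland, NY Binghamton, Kansas and/or Florida", drawn from a list supplied by Human Resources. Section 8.2 (Procedures) has all Associates identified in the selected markets emailed beforehand. The script in Section 12.1 inserts a market-specific link and is sent at market time. Taken together, market must be known for each person, in both arms, before the intervention starts. The sections available for review do not say whether randomisation is stratified by market.

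**The concern.** The primary test pools all markets in one two-by-two table. If uptake differs between markets, or between kinds of employee, that variation stays in the error term. The interval is then somewhat wider, and power somewhat lower, than the same 1,450 people could give. The plan already intends to fit an adjusted model and evidently holds at least one candidate covariate for everyone, so the remedy needs neither new data nor new participants. What is at stake is a modest amount of precision in a trial that has little to spare on its own planning figures. The validity of the result is not in question.

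**Working it through.** **Inputs from Section 9.** Control rate 0.20, intervention rate 0.25 (a 5-point difference), 725 per arm, two-sided alpha 0.05, stated power at least 90%.

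**Step 1: the plan's own power figure.** Power = Φ{[d − 1.96·√(2·p̄(1−p̄)/n)] / √([p₁(1−p₁) + p₂(1−p₂)]/n)}, with d = 0.05 and p̄ = 0.225.

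- Null standard error: √(0.34875/725) = 0.02193; times 1.96 = 0.0430.
- Alternative standard error: √((0.16 + 0.1875)/725) = 0.02189.
- Power = Φ[(0.0500 − 0.0430)/0.02189] = Φ(0.32) = **62.6%**.

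The stated 90% does not reproduce. Unpooled and arcsine versions give 62.7%. For 90% power, 1,464 per arm are needed (2,928 in total). With 1,450 in each arm power is 89.7%, so the planned total looks like a per-arm number. That is a fault of the sample-size statement and has nothing to do with the choice of test.

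**Step 2: what adjustment could add.** As an approximation, covariates that explain a share R² of outcome variance act like a per-arm size of 725/(1 − R²). The documents give no R², so a range is assumed. The extra participants are 1,450/(1 − R²) − 1,450.

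| Assumed R² | Power | Equivalent extra participants (total) |
|---|---|---|
| 0 | 62.6% | 0 |
| 0.02 | 63.4% | 30 |
| 0.03 | 63.9% | 45 |
| 0.05 | 64.8% | 76 |
| 0.10 | 67.1% | 161 |

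Reaching 80% power would need R² of 1 − 725/1,094 = 0.34. Reaching 90% would need 1 − 725/1,464 = 0.50.

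**Step 3: market alone.** R² is the variance of the market rates divided by 0.20 × 0.80 = 0.16. Five equal markets and the control rates below are assumptions.

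- 15/17.5/20/22.5/25%: 0.00125/0.16 = 0.008.
- 10/15/20/25/30%: 0.005/0.16 = 0.031.
- 5/10/20/30/35%: 0.013/0.16 = 0.081.

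**Step 4: simulation check.** For each pattern, 20,000 simulated trials with five equal markets compared the chi-square with a Cochran-Mantel-Haenszel test stratified by market.

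| Control rates by market | Chi-square | Stratified |
|---|---|---|
| All 20% | 62.9% | 62.8% |
| 10/15/20/25/30% | 62.9% | 63.7% |
| 5/10/20/30/35% | 62.1% | 65.3% |

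Type I error in the widest pattern was 5.2% (chi-square) and 5.0% (stratified). The stratified test gains about 1 to 3 points when market is prognostic and loses essentially nothing when it is not.

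**Step 5: interval width.** The unadjusted 95% half-width is 1.96 × 0.02189 = 4.29 percentage points. At R² = 0.031 it is 4.29 × √0.969 = 4.22 points.

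**The case against.** The strongest reply is that nothing here is wrong. An unadjusted chi-square is a valid test in a two-arm individually randomised trial. Chance imbalance in market mix is already allowed for in its error rate. Section 9 also plans checks of randomisation success and an adjusted model, so the proposal mostly exchanges the primary and supporting analyses for a gain that may be near zero. All of this stands, and it is why the point is a minor improvement.

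Several stronger readings are tempting, and the documents do not support them.

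- **That the chi-square causes the power shortfall, or that adjustment would cure it.** It does neither. The shortfall follows from the sample-size figure, and R² of about 0.50 would be needed to close it.
- **That the protocol itself reports different uptake between the trial's markets.** Section 4 (Background) says that case numbers "increased rapidly, specifically in states with lower vaccination rates, many of which are served by Ascension Health facilities". That concerns vaccination rates across states, not documented uptake over a few weeks among employees still without documentation under a mandate. It makes market a reasonable candidate covariate but is no measure of its strength.
- **That Human Resources fields are on file for everyone and that market is already in the adjusted model.** The plan speaks only of "fitting a fully adjusted model with available participant characteristics". No field is listed. That market is held is an inference, though a firm one, from Sections 5.1, 8.2 and 12.1. The number of markets is not fixed either.
- **That the robustness model would yield a conditional odds ratio and so could not confirm the primary result.** The plan names no model. Even if it were a logistic model, the conditional odds ratio under the two wider market patterns would be about 1.35 or 1.37, against a marginal (0.25/0.75)/(0.20/0.80) = 1.33. That gap would not defeat a robustness check.

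**Conclusion.** The point holds as a small, near-free improvement. The gain is about 1 to 4.5 points of power for assumed R² of 0.02 to 0.10, and nothing if the covariates are not prognostic. Market alone gives about 1 to 3 points under the two wider assumed patterns. These figures rest on the plan's 20% and 25% rates, 725 per arm, the variance-reduction approximation in Step 2 and, for market, five equal-sized markets. The documents supply neither the R² nor the market rates, so it cannot be said as fact that precision is being lost, only that it would be if market or other baseline fields predict uptake. No bias and no inflation of type I error is claimed. The change is worth making because it costs so little and because the likely loss, if the covariates prove uninformative, is negligible.

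**What to change.** First correct the sample-size or power statement in Section 9 as a separate matter, since adjustment will not stand in for it.

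Then amend the primary analysis in Section 9 along these lines:

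- Fit a logistic regression of vaccinated (yes/no) on arm, market as a fixed factor, and a short named list of baseline fields that are complete for every participant.
- Fix the list before outcome data are extracted.
- Report the standardised (marginal) risk difference with its 95% CI and p-value, so that the result is on the percentage-point scale used for planning.
- If market is the only complete field, use instead the Cochran-Mantel-Haenszel test stratified by market, with the Mantel-Haenszel risk difference.
- Keep the unadjusted chi-square as the supporting analysis and report it alongside.

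The cost is one or two sentences in Section 9 and slightly more programming, with no new data or participants. The one drawback is that the headline result comes from a model rather than a simple two-by-two table; reporting the chi-square beside it largely answers that.

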### 3.2 Secondary outcome

Time to COVID-19 vaccination in days within 4 weeks of the intervention.

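### The time-to-vaccination analysis names a t-test and a Mann-Whitney test but no rule for people never vaccinated in the window; if only the vaccinated are compared, an uptake gain is missed and the result can reverse

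*Combined protocol and SAP*

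**What the plan says.** Section 3.2 defines the secondary outcome as "Time to COVID-19 vaccination in days within 4 weeks of the intervention". Section 9 gives its analysis: "Differences in time to vaccination will be evaluated using a t-test for means and Mann-Whitney test for medians". The same section states the analysis principle: "All analyses will be evaluated using an intention-to-treat approach".

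Section 9 also supplies the only planning figures. On the control rate: "This assumes a 20% vaccination rate in the control group". The sample is sized "to detect a 5 percentage point difference in vaccination between the intervention and control groups", which implies 25% in the intervention arm, with 725 people per arm.

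No section assigns a time, a censoring rule or an exclusion rule to people not vaccinated by the end of the window. No Kaplan-Meier estimate, log-rank test or Cox model is named. The covariate-adjusted robustness model in Section 9 is of unstated type, so it does not fill the gap.

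**The concern.** A t-test or a Mann-Whitney test needs a value for every person it compares. Most participants may have none, so neither test can be run until someone decides how the unvaccinated enter. If that decision is made after the data are seen, it can change the conclusion.

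There are two obvious readings:

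- **Vaccinated only.** The comparison is then between groups selected by an outcome that the intervention is meant to change. That is no longer a randomised comparison and conflicts with the intention-to-treat statement. It asks whether those who were vaccinated were vaccinated sooner, not whether the intervention sped up vaccination.
- **Unvaccinated set to the last day.** Everyone is kept, but the comparison of medians may carry no information.

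The objective in Section 2 covers both higher and faster vaccination. This outcome is the only one that addresses the second part.

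**Working it through.** **Inputs from Section 9.** 725 per arm; 20% versus 25%; two-sided alpha 0.05. The window is 28 days (Section 3.2). The documents give no distribution of vaccination times, so every timing pattern below is an assumption.

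**The plan's own figure.** Section 9 gives no power for the time outcome. For the primary comparison it claims that 725 per arm "will provide at least 90% power". With pooled variance:

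- SE under the null = √(2 × 0.225 × 0.775 / 725) = 0.02193.
- SE under the alternative = √((0.16 + 0.1875) / 725) = 0.02189.
- Power = Φ((0.05 − 1.96 × 0.02193) / 0.02189) = Φ(0.32) = 62.6%.

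The claim does not reproduce; 90% power needs 1464 per arm. That is a separate matter. Here it means only that about 62% is the natural benchmark for a good time analysis at this sample size.

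**People with no event time.** Control: 725 × 0.80 = 580. Intervention: 725 × 0.75 = 543.75. Together 1123.75 / 1450 = 77.5%. A vaccinated-only test would compare about 145 with about 181 people.

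**Two assumed scenarios,** each with 20% versus 25% vaccinated by day 28:

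- (a) Constant hazards: −ln(0.80)/28 in control and −ln(0.75)/28 in intervention.
- (b) The intervention delays nobody. It adds 5 points by vaccinating 6.25% of those otherwise unvaccinated (0.0625 × 0.80 = 0.05), at times uniform on days 10 to 28.

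Share of simulated trials with p < 0.05 (at least 2,000 trials; repeat runs differed by 1 to 3 points):

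| Analysis | (a) | (b) |
|---|---|---|
| t-test, vaccinated only | about 6% | about 23%, wrong direction |
| Mann-Whitney, vaccinated only | about 6% | about 22-24% |
| t-test, all randomised, unvaccinated = day 28 | about 52% | about 24% |
| Mann-Whitney, all randomised, unvaccinated = day 28 | about 62% | about 56% |
| Log-rank, all randomised, censored at day 28 | about 62% | about 60% |

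**Check on log-rank in (a), Schoenfeld formula.** Events = 145 + 181.25 = 326.25. Hazard ratio = ln(0.75)/ln(0.80) = 1.289, with logarithm 0.254. Power = Φ(√326.25 / 2 × 0.254 − 1.96) = Φ(0.33) = 63%.

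**Check on the reversal in (b).** The control hazard is 0.2231/28, so its reciprocal is 125.48 days. The mean time among vaccinated controls is 125.48 − 28 × 0.80/0.20 = 13.48 days. The added vaccinations average day 19. The vaccinated-only mean in the intervention arm is (0.20 × 13.48 + 0.05 × 19) / 0.25 = 14.58 days, which is 1.1 days later. Over everyone randomised, mean time truncated at day 28 is 0.05 × (28 − 19) = 0.45 days shorter with the intervention. The same data-generating process therefore gives opposite signs.

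**Sensitivity to timing, vaccinated-only t-test.**

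- Added vaccinations on days 15-27, the rest on days 1-14: 2.7 days later with the intervention; 99.8% significant in the wrong direction.
- The same with the rest on days 1-21: 2.0 days later; 79% in the wrong direction.
- Added vaccinations on days 3-8, the rest on days 1-27: 1.7 days earlier; 52% significant, none in the wrong direction.

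**Sensitivity to 4-week uptake, unvaccinated = day 28.** At 20% versus 25%, and still at 40% versus 45%, both medians are 28. At 55% versus 60% they are about 25 and 23 days.

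**The case against.** The best defence is that the plan never restricts this analysis to vaccinated people. The intention-to-treat sentence points to keeping everyone, which leads to setting the unvaccinated to the last day. Mann-Whitney compares ranks, not sample medians. With the unvaccinated tied at one common fixed day and nobody's follow-up ending sooner, it is valid, rejects about 5% under the null, and almost matches log-rank. The t-test on the same data is a valid comparison of truncated mean time, only weaker. All of this stands.

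It limits several stronger inferences that a reader might draw:

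- *The question of speed cannot be answered.* Not supported: one of the two named tests, applied to everyone, answers it nearly as well as log-rank.
- *The plan will point the wrong way.* Not supported as a general statement: reversal needs both the vaccinated-only reading and late gains. Sections 8.2 and 12.1 fit either timing. A reserved date with reminders favours early gains; re-reserving non-attenders for the following Monday favours late ones.
- *Three quarters or more will lack an event time at 4 weeks.* Not stated: the 20% and 25% belong to the primary endpoint, which has a shorter window.

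What the defence does not supply is the missing rule. The vaccinated-only reading is not excluded, and a reference to medians does not suggest that a capped rank test was intended.

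**Conclusion.** The point holds in this form: the plan names two tests that do not handle censoring, for an outcome many participants will not have, and leaves the decisive choice open. Under the vaccinated-only reading, a real uptake gain is all but invisible (about 5-6% rejection against about 62% for log-rank under constant hazards), and late gains can produce a significant result in the wrong direction (about 23% in scenario (b)). Under the last-day reading, medians are uninformative below 50% uptake in both arms and the t-test has about 52% and 24% power, while Mann-Whitney keeps about 62% and 56%.

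The simulated figures rest on 725 per arm, the primary-endpoint rates carried to day 28, and assumed timing. The primary chi-square comparison is untouched. This should be fixed, but it does not undermine the trial's main result.

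**What to change.** 1. Make the main time analysis a time-to-event analysis of all randomised participants: Kaplan-Meier cumulative vaccination curves, a log-rank test, and a Cox hazard ratio or a difference in restricted mean time.
2. Use the same launch date as time zero in both arms. Section 3.2 counts from the intervention, which gives controls no start date of their own.
3. State one common administrative censoring day. Three passages must first be reconciled: the 4-week outcome (Section 3.2), follow-up to 2 weeks after the first appointment week, so about 3 weeks (Section 5.2), and the possible roll-out to controls about 2 weeks later (Section 8.2). The power figures above assume day 28 and no earlier roll-out; an earlier day would change them.
4. State whether the event date is the dose date or the upload date. Section 9 classifies people by upload of documentation, while the secondary outcome concerns vaccination.
5. Mann-Whitney with the unvaccinated tied at the censoring day may stay as a supporting test. Label vaccinated-only times as descriptive.

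The cost is plan wording and standard software, with no extra participants. If only upload dates are held, dose dates would also have to be extracted.
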